## Abstract

**Background**: While primary health care (PHC)-based prevention and management of heavy drinking is clinically effective and cost-effective, it remains poorly implemented in routine practice. Systematic reviews and multi-country studies have demonstrated the ability of training and support programmes to increase PHC-based screening and brief advice activity to reduce heavy drinking. However, gains have been only modest and short term at best. WHO studies have concluded that a more effective uptake could be achieved by embedding PHC activity within broader community and municipal support.

**Protocol**: A quasi-experimental study will compare PHC-based prevention and management of heavy drinking in three intervention cities from Colombia, Mexico and Peru with three comparator cities from the same countries. In the implementation cities, primary health care units (PHCUs) will receive training embedded within ongoing supportive municipal action over an 18-month implementation period. In the comparator cities, practice as usual will continue at both municipal and PHCU levels. The primary outcome will be the proportion of consulting adult patients intervened with (screened and advice given to screen positives). The study is powered to detect a doubling of the outcome measure from an estimated 2.5/1,000 patients at baseline. Formal evaluation points will be at baseline, mid-point and end-point of the 18-month implementation period. We will present the ratio (plus 95% confidence interval) of the proportion of patients receiving intervention in the implementation cities with the proportions in the comparator cities. Full process evaluation will be undertaken, coupled with an analysis of potential contextual, financial and political-economy influencing factors.

**Discussion**: This multi-country study will test the extent to which embedding PHC-based prevention and management of alcohol use disorder with supportive municipal action leads to improved scale-up of more patients with heavy drinking receiving appropriate advice and treatment.

**Study status**: The four-year study will start on 1
^st^ December 2017.

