### Data collection

Based on the validated methodology of the ODHIN project
^41,
122^, PHC providers will document activity by completing paper or electronic (depending on the ability to use existing electronic health records) anonymous tally sheets that record eligible patients’ (aged 18+ years) AUDIT-C scores, if administered, DSM-5 11-item and PHQ-9 scores, and the advice or treatment given to each patient. The tally sheets will record the age, sex, employment status, and educational level of the patient, the latter as one proxy measure of socio-economic status. The tally sheets will also include: two questions that capture previous experience of being asked about how much the patient drinks and of being advised to reduce the amount drunk to provide information for UN Sustainable Development Goal 3.5
^12^; one question about alcohol being a cause of high blood pressure, liver problems, depression or cancer, as a simple measure of alcohol health literacy (knowledge part)
^123^; and, two questions about injunctive social norms of drinking alcohol
^124^.

Data will be collected for each calendar month during the 18-month scale-up period. Formal evaluation will take place during three measurement periods: 4-week baseline period; 4-week assessment period during the 9
^th^ month of the 18-month scale-up period; and, 4-week assessment period at 18-months, the end of scale-up period. PHCUs will return data on the number of adult (aged 18+ years) consultations per provider for the four-week baseline assessment period, and for each of the 18 months of the scale-up period.

At baseline, PHC providers will provide data on their age, sex and profession (doctor, nurse, practice assistant etc.). At baseline, and at two time points during the 18-month scale-up period (month 4.5 and month 13.5), providers will provide data on their alcohol health literacy and on their attitudes to working with patients with heavy drinking. The alcohol health literacy instrument will assess knowledge of risks due to drinking
^123^, and descriptive and injunctive social norms
^124^. The attitudes instrument will be the shortened version of the Alcohol and Alcohol Problems Perception questionnaire
^125^.

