### Outcomes

**Primary outcome:** The primary outcome will be the proportion of consulting adult patients intervened (screened and advice given to screen positives), calculated as the number of AUDIT-C positive patients that received oral advice or referral for advice to another provider in or outside the PHCU, divided by the total number of adult consultations of the participating providers per provider and per PHCU.

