### Sample size

Our power calculations are based on the following assumptions: at baseline, 2.5/1,000 consulting patients will be found to be screen positive (based on an AUDIT-C cut-off score of 8) and advised to reduce their alcohol consumption (data from ODHIN study; [name], personal communication). To detect an increase in the number to 5/1,000 (a doubling), with 80% power and a significance level of 5%, and assuming a design effect of ten PHCUs per three cities per group (scale-up and comparator), with an ICC for PHCUs across countries = 0.03 (data from ODHIN study; [name], personal communication), a conservative estimate of 30 PHCUs across three scale-up cities and 30 across three comparator cities, about ten per city will be needed
^150^, assuming an average PHCU size of about 8,000 patients with a monthly consultation rate of 1,200 adult patients per PHCU (data from ODHIN study; [name], personal communication).

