### Statistical measures

The primary outcome of the study will be the proportion of consulting adult patients intervened (screened and advice given to screen positives) measured during two four-week periods midway and at the end of the 18-month scale-up period, and this will be analysed at the levels of the PHCU and provider by city type (intervention or control)
^151^. Given the rarity of the event and the resulting distribution, we will use exact inference methods for comparison of intervention vs. control cities. For further analyses, including covariates, regression models will be used, taking into consideration the hierarchical nature of the data
^152^, and characteristics at different hierarchy levels (i.e., characteristics of the PHCU, characteristics at the city level, such as patterns of drinking), and incorporating 4-week baseline period measurements as covariates. Special consideration will be given to the skewness of data by applying models, such as zero-inflated binomial regression, after testing for necessary assumptions
^153,
154^. Odds ratios will be presented with 95% confidence intervals. For any PHCU or provider that drops out during the study, outcome values for subsequent measurement points will be set at the last value obtained.

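### Carrying the last value forward after dropout assumes unchanged activity up to month 18 and counts imputed values as observed; the size of the bias is unknown and its direction is not fixed

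*Protocol article*

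**What the plan says.** The protocol article, under Statistical measures, gives one rule for dropout: "For any PHCU or provider that drops out during the study, outcome values for subsequent measurement points will be set at the last value obtained". It closes the paragraph on the primary outcome, which is "measured during two four-week periods midway and at the end of the 18-month scale-up period". It therefore governs the month-18 value and, for those who leave early, the mid-point value too. It applies to both groups and does not depend on the reason for leaving. The only other missing-data rule in the article, under Outcomes, fills in single items of the provider attitude scale.

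Three further statements bear on it.

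- Under Outcomes, the primary rate is the number of screen-positive patients who were advised or referred, "divided by the total number of adult consultations of the participating providers per provider and per PHCU".
- Under Data collection: "Data will be collected for each calendar month during the 18-month scale-up period". Consultation numbers are also returned for each of the 18 months.
- Under Statistical measures, the main comparison uses exact methods. Hierarchical regression with baseline as a covariate is planned for further analyses.

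The Discussion lists the 18-month frame as a feature of the study because it allows longer-term effects to be assessed.

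**The concern.** LOCF gives the right answer only if activity stays at the carried level after a unit leaves. Whether activity holds up to month 18 is what the last measurement is there to show, so for leavers the rule supplies the answer by assumption.

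Two things are at stake. The first is the month-18 estimate: a mid-point value carried over a period in which others fade hides that fading, while a baseline value carried over a period in which others improve hides the improvement. The second is precision: carried values enter the comparison as if they had been measured.

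The rule is also open to two readings. With monthly data and three formal measurement periods, the value carried could be that of the last month reported or of the last formal period, and the results can differ.

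**Working it through.** The plan has no dropout figure to reproduce, so the check asks what LOCF would report under stated scenarios.

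**Inputs.** From the Sample size section: a rate of 2.5 per 1,000 ("at baseline, 2.5/1,000 consulting patients will be found to be screen positive" and advised), a target of 5 per 1,000, 30 PHCUs per group and 1,200 adult consultations per PHCU per month. Assumed, because the article does not give them: dropout *d* of 10% to 30%, a fade among intervention stayers from 5 at month 9 to 3 at month 18, control stayers constant at 2.5, PHCUs of equal size, and the formal-period reading of the last value.

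**Formula.** Group rate at month 18 = (1 − d) × stayers' rate + d × leavers' rate. LOCF puts the carried value in place of the leavers' rate.

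**1. Late leaving, equal in both groups, gains fading among stayers.**

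- d = 20%, LOCF: intervention 0.8 × 3 + 0.2 × 5 = 3.4; control 2.5; ratio 3.4/2.5 = 1.36.
- Truth if leavers behave like stayers: 3.0/2.5 = 1.20.
- Truth if leavers stop in both groups: (0.8 × 3)/(0.8 × 2.5) = 2.4/2.0 = 1.20.
- d = 30%, LOCF: 0.7 × 3 + 0.3 × 5 = 3.6; ratio 3.6/2.5 = 1.44. Truth: 3.0/2.5 = 1.20, or 2.1/1.75 = 1.20.

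**2. Late leaving, with the gain gone in everyone by month 18 (true ratio 1.00).** LOCF gives (0.9 × 2.5 + 0.1 × 5)/2.5 = 1.10 at 10%, and in the same way 1.20 at 20% and 1.30 at 30%.

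**3. Late leaving, stayers holding 5 against 2.5.** LOCF always reports 2.00.

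- 20% of each group leaves and goes back to 2.5: truth (0.8 × 5 + 0.2 × 2.5)/2.5 = 1.80.
- 20% of each group leaves and stops: truth 4.0/2.0 = 2.00, so the ratio is unbiased. The difference is overstated, at 2.5 against 2.0 per 1,000.
- 30% intervention and 10% control leave and stop: truth 3.5/2.25 = 1.56.
- 10% intervention and 20% control leave and stop: truth 4.5/2.0 = 2.25, so LOCF understates.

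**4. Early leaving (before month 9), baseline carried, 20% in each group, stayers at 5 against 2.5.** LOCF gives (0.8 × 5 + 0.2 × 2.5)/2.5 = 1.80. Truth is 1.80 if leavers stay at baseline, but 2.00 if they would have done as stayers do (5.0/2.5) or if they stop in both groups (4.0/2.0).

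**5. Precision.** In scenario 1 at 20%, 6 of 30 intervention PHCUs leave. LOCF supplies 6 × 1,200 = 7,200 consultations that nobody observed, with 7,200 × 5/1,000 = 36 events. The 24 stayers contribute 24 × 1,200 × 3/1,000 = 86.4. So 36 of 122.4 events (29%) are imputed and counted as data.

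**The case against.** The strongest reply is that the bias has neither a known size nor a fixed sign. That stands. The rule covers both groups; scenario 3 includes a case with no bias in the ratio and one in which LOCF understates, and scenario 4 is neutral or conservative. If the last value means the last month reported, the carried value can be more recent than the last formal period and the distortion in scenario 1 may be smaller.

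Several stronger readings are tempting, and the documents do not support them.

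- A reader might infer that LOCF can turn a loss into a gain: 1.36 reported against 2.4/2.5 = 0.96 at 20% dropout, or 1.44 against 2.1/2.5 = 0.84 at 30%. Those truths need dropout in the intervention group only. With equal dropout the truth is 1.20.
- A reader might take "However, gains have been only modest and short term at best" as the trial's own premise that gains fade. The sentence describes earlier training and support programmes. The stated hypothesis is a higher proportion screened and advised than in provider-only studies, and municipal support continues throughout.
- A reader might take month 9 as the peak. No peak is given, and the booster sessions may fall at any time in the first twelve months, so one could come after month 9.
- A reader might assume that a withdrawn unit delivers nothing. The outcome comes from study tally sheets, so a unit may stop the paperwork and go on advising.

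It may also be said that a fuller analysis plan could add sensitivity analyses. It could, but the carry-forward rule is stated outright and without qualification.

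**Conclusion.** The concern holds in a limited form. The rule fixes, for the primary outcome, an assumption of constant activity after dropout that the month-18 measurement should examine, and it understates uncertainty. Under an assumed fade from 5 to 3 per 1,000 with equal late dropout, it overstates the ratio by 0.16 at 20% dropout (1.36 against 1.20) and by 0.24 at 30% (1.44 against 1.20). These figures depend on the assumed rates, on the assumed dropout and on the month-9 value being the one carried; they are not a forecast. The documents do not show that LOCF favours the intervention in general.

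**What to change.** Delete the LOCF sentence and replace it with three statements.

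1. The exact comparison uses the PHCUs and providers observed at each measurement point.
2. The month-18 contrast is estimated from the planned hierarchical model, fitted to all observed PHCU-months with no single-value imputation.
3. Sensitivity analyses, applied to both groups alike, set activity after dropout to the baseline rate and to zero.

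No new data are needed, because monthly activity and consultation numbers are already to be collected.

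The change is more than one of wording. It gives a model now listed for further analyses a larger role beside the exact comparison. The model-based contrast relies on data being missing at random given earlier months, which the sensitivity analyses probe but do not test. The observed-only comparison has its own limit: in scenario 1 it gives 3.0/2.5 = 1.20, as it should, but with 10% against 20% dropout to zero in scenario 3 it gives 5/2.5 = 2.00 against 2.25, no better than LOCF. The set-to-zero analysis also needs a denominator, such as the last known consultation volume, which is artificial for a provider who has left the job.

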### Ethics

Before any involvement of participants in the study, including patients consulting in the study PHC units, the respective country-based partner in Colombia, Mexico and Peru will comply with their national legislation, regulations and ethical principles by applying for an ethical approval for research at the competent ethical authorities in their jurisdiction.

## Discussion

This protocol outlines a quasi-experimental study
^84^ to test the extent to which embedding PHC-based screening and brief advice activity within supportive municipal action leads to improved scale-up of more patients with heavy drinking receiving appropriate advice and treatment.

For a wide range of health care issues, including communicable and non-communicable diseases, as well as reproductive and child health care, major variations continue to exist in many dimensions of quality of care, including safety, efficiency, effectiveness, timeliness, patient centeredness, and equity
^70^. This can be understood as a failure to equitably scale up excellent care to ensure that what we know works is delivered to everyone who needs it.

There is a wealth of literature on implementation science and quality improvement, and a range of frameworks exist that include a sequential approach for scale-up, and that provide practical guidance for how to work with organizations, health systems, and communities to implement and scale-up best practices
^76–
83^.

In choosing a framework to adopt and apply, we wanted one that draws together: the main themes of sequencing activities to get a complex health system intervention, with elements of prevention and management, to full scale; the mechanisms that are required to facilitate the adoption of a complex health system intervention; and, the underlying factors and support systems required for successful scale-up. We also wanted a framework that includes a scalable unit at meso- (in our case city) level that provides the key infrastructural components and relationship architecture that are likely to be common across cities that are part of networks, (e.g., Healthy Cities Networks) enabling a more likely successful transition to full scale.

A key framework that meets all these needs is that of the Institute for Healthcare Improvement (IHI) which identifies adoption mechanisms and support systems for use across the steps, and identifies the implementation methods that can be used at each step, that we have incorporated into our protocol
^70^.

The proposed study has several features that merit attention.

First, we simplify and account for cultural differences in definitions of AUD
^18,
19^, by using heavy drinking
^20,
21^ as our operational approach, rather than AUD or harmful use of alcohol
^1–
3^.

Second, we set a higher cut-off score for AUDIT-C (8+) than is commonly used to classify screened case-positives, matching definitions of heavy drinking
^23,
24^, and similar to baseline levels of alcohol consumption in PHC-based trials to reduce heavy drinking
^59^. We also set the same cut-offs for men and women, based on epidemiological evidence
^24^, and minimizing unintended consequences of using different cut offs for men and women
^155^.

Third, we limit brief advice to 5-10 minutes, rather than using more intensive interventions
^67^, since the evidence suggests that brief advice is as effective and cost-effective as more extended advice or treatment in reducing heavy drinking
^33,
34,
156,
157^.

Fourth, we recognize the importance of comorbid moderately severe and severe depression
^65,
66^, by building in identification and referral mechanisms, recognizing that moderately severe and severe depression can be well-managed with sufficient support systems in PHC
^67–
69^.

Fifth, based on evidence
^71^, we adopt a novel approach by embedding and scaling-up the PHC activity within cities, supported by a series of city-based adoption mechanisms and support systems
^70^, and enhanced alcohol health literacy
^158^, aiming to assist in building a new knowledge base, on which better policy could be based.

Sixth, we use a theory-based approach to tailoring
^100–
102^, creating city-based Community Advisory Boards, and user-based UPs to ensure that tailoring matches user needs, municipal services
^103^, and co-production of health
^93,
104^.

Seventh, we include a range of outcome measures, including patient outcomes, as a quality check
^126^, which address weaknesses of many previous implementation studies in this area, which have focussed on provider outcomes, rather than patient outcomes
^42,
43^. Through the use of existing electronic health records, and further to ethical and confidentiality agreements, we anticipate the ability to link individual AUDIT-C scores with consultations within the primary health care centers and hospitalizations within district hospitals, recording diagnosis for both fully and partially attributable alcohol-related conditions
^13^.

Eighth, we have a longer time frame (18 months) than is traditionally used in implementation studies
^41,
44,
45,
159^, to assess longer term impacts.

Ninth, we give considerable emphasis to process evaluation
^144^, developing logic models to document the fidelity of all implementation strategies, and to identify, the drivers and barriers and facilitators to successful implementation and scale-up, and the political and economic contextual factors that might influence scale-up, based on the RE-AIM framework
^138^.

And, finally, tenth, we place the study design in the public domain, so that others might replicate the study approach (with acknowledgment) to see if the scale-up principles can work across jurisdictions. In so doing, we would be pleased to receive comment and feedback.

We are aware of some limitations of the study design. As we are unable to randomize the involved cities, we adopt a quasi-experimental design, recognizing that it is not possible to randomly allocate the municipalities. Randomized selection of the municipalities was excluded as the hypotheses and the study approach relies on municipal-level interventions. A trial with random assignments of municipalities is not feasible due to cost (number of municipalities) and municipal-based political and technical considerations. Randomization of primary health care centers within municipalities is also impossible for the same reasons of municipal involvement in the interventions. Clean control conditions in this environment where the municipality supports primary health care-based does not seem to be possible. As a result, we created a quasi-experimental design
^84,
160,
161^, trying to optimize control for confounding, and using propensity score matching (PSM), given the above constraints. While full control via randomization, and thus establishment of causality is not possible, together with the qualitative evaluation component of the study, we will be able to clearly identify the mechanisms which were crucial in leading to the outcomes. According to a recent 7-item checklist for classifying quasi-experimental studies for Cochrane reviews
^162^, our approach is, nevertheless, ranked as a strong design.

Although our focus on embedding PHC activity within supportive municipal actions is hypothesized to increase screening and brief activity over and above that previously demonstrated, such an approach also brings risks. Municipal governments change; and, thus health priorities may change. Although our approach minimizes the need for extra resources (and in some jurisdictions, could be resource saving
^34,
40^), it is not resource free. Funding constraints could limit future scale-up and sustainability.

We have adopted two approaches to promote sustainability. First, our protocol is based on transdisciplinary research, which is an approach that: identifies, structures, analyses, and deals with specific problems in such a way to grasp the complexity of problems
^163^; takes into account the diversity of life-world and scientific perceptions of problems; links abstract and case-specific knowledge; and, develops knowledge and practices that promote what is perceived to be the common good
^164^. As such, we involve municipalities as stakeholders to form explicitly orchestrated and managed ecosystems that cross organizational boundaries. Municipalities will create an appropriate engagement platform that provides the necessary environment, including people and resources, for sustainability. Second, we have chosen municipalities as the level of scale, making use of the existing Latin American and Caribbean (LAC) Healthy Cities Network as a natural platform for going to full-scale.
